#### 1.1.4. Qualitative interviews

A subsample of the study participants (N = 8 - 10) will be asked to participate in qualitative interviews on their experience of internet-delivered CBT. The interviews are held in an open, information generating manner with few, open questions, such as “How did you experience ICBT?” and “What did you find helpful in the treatment, what could have been better?” The interviews will be taped and transcribed and then rated by experienced clinical psychologists trained in qualitative method. The material is then summarized into themes and dimensions that can be generalized from the interviews. The general dimensions as well as exemplifying quotes will be presented as a result from this qualitative study.

## 1.2. Procedure

For recruitment, the project will be advertised in media, mental health services, primary care and schools. Inclusion procedures will be carried out in two steps: telephone interview and face-to-face assessment. Figure 1 gives an overview of the inclusion, assessment and treatment procedures.

### 1.2.1. Telephone interview

An initial telephone interview will be conducted with the parent/primary caregiver in order to assess broad inclusion and exclusion criteria. Participants will be interviewed with the MINI-KID

screening items for OCD, which means asking the parent about the adolescents' obsessions and compulsions on a general level.

Inclusion criteria on this stage are:

- age between 12 and 17 years
- ability to read and write Swedish
- daily access to the internet
- a parent that is able to co-participate in the treatment
- Participants on psychotropic medication must have been on a stable dose for the last 6 weeks
- Suspected or likely compulsions or obsessions on the MINI-KID OCD screening

Subjects will be excluded on this stage if:

- subject not able to read or understand the basics of the ICBT self-help material
- psychotropic medication changes within 6 weeks prior to treatment
- completed CBT for OCD within last 12 months
- ongoing psychological treatment for OCD or another anxiety disorder
- Absence of compulsions and obsessions on the MINI-KID OCD screening
- presence of an autism spectrum disorder, psychosis/schizophrenia or bipolar disorder

### **1.2.2. Face-to-face baseline diagnostic assessment**

After telephone screening participants are invited to a face-to-face assessment, including the diagnostic screening interview MINI-KID jointly with both the adolescent and parent. If MINI-KID indicates OCD, adolescent and parent will be interviewed jointly with CY-BOCS to assess OCD severity with respect to cut-off for inclusion (total score of  $> 15$ ). Following face-to-face assessment, participants meeting inclusion criteria will be provided with an information sheet and consent form.

Inclusion criteria on this stage are:

- a primary diagnosis of OCD as defined by DSM-IV TR
- CY-BOCS total score  $> 15$
- signed informed consent

Subjects will be excluded if:

- presence of an autism spectrum disorder, psychosis/schizophrenia or bipolar disorder
- suicidal ideation

- ongoing substance dependence
- CY-BOCS total score < 16

### **1.2.3. Baseline self-report measures**

Participants included in the study after face-to-face diagnostic assessment will be asked to fill in self-report measures on the internet, provided via personal log-in.

### **1.2.4. Treatment**

When completed the self-report measures adolescents and parents will be provided with login information for the ICBT treatment platform. Adolescents and parents will have separated login accounts. From the start of treatment participants will have full-scale access to the internet treatment for 12 weeks, which includes materials, interactive scripts and mail contact with a clinician. After 12 weeks participants will have access to treatment materials, but it will not be possible to unlock new parts of the treatment or to have email contact with the clinician.

### **1.2.5. Weekly assessment of OC symptom severity**

Participants will be assessed with the CHOCI-R parent and child version once a week to monitor treatment progress.

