### **3. Method**

#### **3.1. Subjects**

Inclusion of participants compromise the following criteria:

- a primary diagnosis of OCD as defined by DSM-IV TR
- a total score of above 15 on the CY-BOCS
- age between 12 and 17 years
- ability to read and write Swedish
- daily access to the internet
- a parent that is able to co-participate in the treatment
- Participants on psychotropic medication must have been on a stable dose for the last 6 weeks prior to baseline assessment
- signed informed consent

Subjects will be excluded if:

- diagnosed autism spectrum disorder, psychosis or bipolar disorder
- suicidal ideation
- ongoing substance dependence
- subject not able to read or understand the basics of the ICBT self-help material
- completed CBT for OCD within last 12 months (defined as at least 5 sessions CBT including exposure and response prevention)
- ongoing psychological treatment for OCD or another anxiety disorder

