*Adverse events assessment.* During the treatment phase of the study participants will be asked to fill in a web-based form on the occurrence of any adverse events as a reaction to or consequence of the treatment. Adverse events frequency will be reported in the publication of the study.

In the self-report procedure parents will even be asked to answer questions about parental educational level and gross household income, ethnicity of adolescent and parents and other demographic data. Moreover, participants will be asked about prior treatment history (e.g. previous CBT or medication) and response to previous treatments. Table 1 gives an overview of the measures that will be used in the study. Attachment 1 displays an overview of which measures are used when in the study.

Table 1: List of measures

| Category                        | Clinician assessed                          | Self-report adolescent | Self-report parent                                       |
|---------------------------------|---------------------------------------------|------------------------|----------------------------------------------------------|
| Demographics             | Age
Sex
Family structure              |                        | Educational level
Gross household income
Ethnicity |
| OC symptom severity      | CY-BOCS
CGI-S
CGI-I                   | CHOCI-R
COIS-R      | CHOCI-R
COIS-R                                        |
| Comorbidity              | MINI-KID                                    | SCAS
SDQ
CDI     | SCAS
SDQ                                              |
| Global functioning       | CGAS                                        |                        |                                                          |
| Parental psychopathology |                                             |                        | GAD-7
PHQ-9
OCI-R                                  |
| Family factors           | Family history of OCD
/ other diagnosis? |                        | FAS-PR                                                   |

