### **1.2.6. Safety procedures**

Clinicians that suspect any kinds of adverse events under the assessment or treatment process contact the parent and adolescent via telephone as a first step of assessing the severity of the incident. Adverse events in this context is defined as an actual or potential situation that threaten the patients well-being e.g. suicide risk. In the case of an adverse event the clinician informs the study coordinator (FL) for discussion of adequate action taking. If prolonged ICBT treatment is considered inappropriate with regard to the participants' best interest and well-being the participant is excluded from the study and both parent and adolescent provided with proper referral information. Any adverse events will be reported in the planned publication of the pilot study.

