### **1.2.8. Post-treatment measurement and follow-up**

Post-treatment measurement with clinician rated symptom severity (face-to-face interview with CY-  
Project plan BiP OCD, version 2014-12-16

BOCS, CGI-I, CGI-S and CGAS) as well as self-report measures will be conducted immediately after treatment, latest within 4 weeks after treatment protocol is finished.

Follow-up measurements will be performed at 3, 6 and 12 months after treatment. At follow-up CY-BOCS, CGI-I, CGI-S and CGAS will be administrated over the phone by a clinician. Self-report measures will be administrated via the internet.

Succeeding completed follow-up all participants will be contacted by the clinician via the ICBT platform and offered an ICBT booster session. Thus, standardized booster sessions will be offered at 3, 6 and 12 months after treatment. During follow up, participants are asked whether they are willing to participate in the qualitative interview study. Participants give consent to this study on a separate form.

[figure not shown]

Figure 1: Procedures flow chart

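### Suicide risk is the only adverse event the protocol names, but the one form that solicits adverse events is limited to the treatment phase and to events attributed to treatment

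*Protocol*

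**What the plan says.** Protocol Section 3.1 excludes candidates with "suicidal ideation", and Section 1.2.2 applies that exclusion at the baseline visit: "After telephone screening participants are invited to a face-to-face assessment, including the diagnostic screening interview MINI-KID jointly with both the adolescent and parent". Neither section says which instrument or question applies it.

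Section 1.2.6 (Safety procedures) gives the definition: "Adverse events in this context is defined as an actual or potential situation that threaten the patients well-being e.g. suicide risk". It requires no link to treatment. Its procedure begins with a clinician's suspicion: "Clinicians that suspect any kinds of adverse events under the assessment or treatment process contact the parent and adolescent via telephone".

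The adverse events paragraph in Section 1.1.3 describes the solicited collection, which is set for the treatment phase: "participants will be asked to fill in a web-based form on the occurrence of any adverse events as a reaction to or consequence of the". (The quote stops one word short of the end of its sentence; the missing word refers to the ICBT.) It does not say how often. Sections 1.1.3 and 1.2.6 both promise that adverse events will be reported in the publication.

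The scheduled measures are these:

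- **Weekly, during treatment** (Section 1.2.5): "Participants will be assessed with the CHOCI-R parent and child version once a week to monitor treatment progress".
- **After treatment** (Section 1.2.8): CY-BOCS, CGI-I, CGI-S and CGAS face to face, plus self-report measures.
- **At 3, 6 and 12 months** (Section 1.2.8): "At follow-up CY-BOCS, CGI-I, CGI-S and CGAS will be administrated over the phone by a clinician", with self-report measures over the internet.

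The MINI-KID is not listed after baseline. The adolescent depression scale (CDI) is one of the web-administered self-reports. Section 1.2.4 ends e-mail contact with the clinician after 12 weeks.

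**The concern.** The definition of an adverse event and the instrument that collects adverse events do not match. The safety section counts any threat to well-being. The form counts only what the respondent sees as produced by the treatment, and only while treatment lasts. An adolescent who becomes suicidal for reasons unrelated to ICBT, or who does so some months after week 12, has an event under the safety section but is not asked for it by the form.

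Two things are at stake. One is the safety result of a pilot meant to inform wider use of remotely delivered treatment in 12- to 17-year-olds: a low or zero count could not be read as a low or zero rate. The other is that no analysis plan can repair this later, because answers that were never collected cannot be analysed.

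**Working it through.** The protocol gives no figure to reproduce, so the check sets its provisions side by side.

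| Route after baseline | Protocol section | Period | Limited to events attributed to treatment? | Described as asking about suicide risk? |
|---|---|---|---|---|
| Web adverse event form | 1.1.3 | Treatment phase | Yes | Only so far as the respondent attributes it to treatment; item content not given |
| Weekly CHOCI-R | 1.2.5 | Treatment | Not applicable | No; described as an OCD severity measure |
| E-mails, calls and program forms | 1.3 | Treatment (12 weeks) | No | Not described |
| Clinician suspicion, then telephone call | 1.2.6 | Assessment and treatment process | No | Acts on suspicion; not a question put to everyone |
| Four clinician assessments | 1.2.8 | Post-treatment; 3, 6 and 12 months | Not applicable | No; OCD severity, global severity or change, functioning |
| Web self-reports, including CDI | 1.1.3, 1.2.8 | Post-treatment and follow-up; the measures at each visit are in an attachment not at hand | Not applicable | CDI item content not given; no route to a clinician stated |

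**Step 1: scope.** Take as the target every event that meets the Section 1.2.6 definition. The form reaches only the part that arises during treatment and is attributed to it. The rest depends on a clinician coming to suspect it.

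**Step 2: time.** Treatment lasts 12 weeks and the last follow-up is 12 months after treatment, about 52 weeks. The total is 12 + 52 = 64 weeks. The form covers at most 12/64 = 19% of that time, and 52/64 = 81% lies outside it. In that 81% the described contacts are three telephone assessments, web self-reports and the booster sessions offered with them.

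**Step 3: direction.** For suicide risk, the recorded events are those caught by the form or by clinician suspicion. That set cannot exceed the true set unless there are false reports. The recorded frequency is therefore at best correct and otherwise too low. For adverse events as a whole the direction is less certain: the form may also pick up minor reactions to treatment that fall outside the Section 1.2.6 definition. The overall figure would mix two definitions.

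**Step 4: size.** The undercount depends on how many events occur, how many respondents attribute them to ICBT, and how often a clinician picks up the remainder. The protocol gives none of these, so no percentage can be put on it.

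**The case against.** The strongest reply is that the protocol does look for adverse events after entry. The web form solicits them, and the safety section's definition includes suicide risk. Section 1.3 provides regular therapist contact by e-mail, telephone and in-program forms. A parent takes part throughout. Clinician suspicion can arise at the post-treatment visit and in the follow-up calls as well as during treatment. Section 3 (Ethical considerations) relies on therapist contact to identify families who need other care.

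That reply stands against the stronger reading. A reader might infer that suicidality would come to light only if a participant volunteered it, or that nobody asks after baseline. The documents do not support this. The form asks during treatment, and therapists are in touch. Nor can one say that no later instrument contains a suicidality item: the contents of the CDI, the web form and the program forms are not given, and the attachment with the full schedule is not in the text at hand.

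A reader might also reach for the upper confidence bound that goes with zero events in 27 participants. That bound holds for any zero count in a sample of this size and does not measure this gap.

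The reply does not remove the mismatch. The form's two limits are in its own wording. The therapist contact of Section 1.3 belongs to the treatment period, and e-mail contact ends with it. A suspicion-led procedure is not the same as asking every participant, and Section 3 itself notes that ICBT changes how much information the therapist receives.

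**Conclusion.** The point holds in this form: no suicidality-specific question with a stated frequency is described after baseline, and the only solicited adverse event collection is narrower than the protocol's own definition in both cause and time. Cover is partial during the 12 weeks of treatment and thinner over the following 52 of about 64 weeks. The promised adverse event frequency would rest on two definitions, and suicide risk within it would tend to be undercounted.

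This rests on reading the form as it is described and on the schedule stated in the body of the protocol. If the schedule attachment or the form itself already asks about suicide risk regardless of cause, at each time point, the gap narrows to an inconsistency of wording. The efficacy analysis is not affected. The change should be made because the safety statement cannot be recovered afterwards and the remedy is small.

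**What to change.** Reconcile Sections 1.1.3, 1.2.6 and 1.2.8 on four points:

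1. **One definition.** Ask about adverse events in the Section 1.2.6 sense, including suicide risk, whatever the respondent believes the cause to be. Record perceived relation to treatment as a separate answer.
2. **Stated occasions.** Give the web form a frequency during treatment, and put the same question at the four clinician assessments already scheduled (post-treatment, 3, 6 and 12 months). Repeating whatever check applied the entry exclusion would be one way.
3. **Route.** State how web-entered answers, from the adverse event form and the CDI, reach the clinicians on whose suspicion the safety procedure depends. What they then do remains for the protocol team.
4. **Reporting.** Give the number positive out of the number asked at each time point, so that a zero can be told apart from a question not put.

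The cost is a short amendment, a change to an existing web form, a few minutes per scheduled contact and slightly more respondent burden.

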### **1.2.6. Safety procedures**

Clinicians that suspect any kinds of adverse events under the assessment or treatment process contact the parent and adolescent via telephone as a first step of assessing the severity of the incident. Adverse events in this context is defined as an actual or potential situation that threaten the patients well-being e.g. suicide risk. In the case of an adverse event the clinician informs the study coordinator (FL) for discussion of adequate action taking. If prolonged ICBT treatment is considered inappropriate with regard to the participants' best interest and well-being the participant is excluded from the study and both parent and adolescent provided with proper referral information. Any adverse events will be reported in the planned publication of the pilot study.

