##### **1.1.2. Diagnostic and symptom severity measures**

*Mini International Neuropsychiatric Interview for Children and Adolescents, MINI-KID* (D V Sheehan et al., 1998) is a short structured diagnostic interview for DSM-IV and ICD-10 psychiatric disorders in children and adolescents. MINI-KID is a reliable diagnostic instrument and is validated against the widely used MINI-KID-PL interview (D V Sheehan et al., 2010).

*Children's Yale Brown Obsessive Compulsive Scale, CY-BOCS* (Scahill et al., 1997). CY-BOCS is a semi-structured clinician administered interview and considered the golden standard in assessment

of OC symptom severity in children and adolescents. CY-BOCS has high internal consistency, good to excellent inter-rater agreement and correlates significantly with self-ratings of OC symptoms (Scahill et al., 1997). CY-BOCS will be the primary outcome measure.

*Clinical Global Impression – Severity, CGI-S* (National Institute of Mental Health, 1985). CGI-S is a brief clinician rating of symptom severity. Ratings on the seven graded scale range from 1 = “no symptoms” to 7 = “extreme severe”. CGI-S correlates highly with the CY-BOCS total score ( $r = .75$ , Storch et al., 2004).

*Clinical Global Impression - Improvement, CGI-I* (Guy, 1976). CGI-I is a brief clinician rating of the patients symptom severity change relative to the basement assessment. The seven graded scale ranges from 1 = “very much improved” to 7 = “very much worse”.

*Children’s Global Assessment Scale (CGAS, Shaffer et al., 1983)*. CGAS is a widely accepted instrument to quantify the overall level of functioning in children and adolescents. The 100-point scale is clinician rated and has demonstrated to have good discriminant and concurrent validity (Shaffer et al., 1983) as well as moderate inter-rater reliability in naturalistic settings (Lundh, Kowalski, Sundberg, Gumpert, & Landén, 2010).

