## **3. Ethical considerations**

ICBT differs from traditional therapy in the amount of information that the therapist is given. A thorough assessment decreases the risk of patients in need of more extensive care being included in the study. The regular e-mail communication, and the possibility for the participating families to contact their therapist if needed, ensures that families with problems too severe for this program will be referred to more suitable treatments. The participants may worry about computer safety and maintenance of confidentiality. The families are provided with information about the risks and precautions that are being taken when using communication technology, e.g. encrypted server technology. International rules and regulations will be followed. In our view, the ethical risk is limited since every study participant will receive treatment.

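### Taking a participant off ICBT also takes them out of the study, so as written their later CY-BOCS is never obtained, which risks overstating improvement in a single-arm trial

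*Protocol*

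**What the plan says.** The rule is in Protocol section 1.2.6 (Safety procedures). A suspected adverse event, defined as "an actual or potential situation that threaten the patients well-being e.g. suicide risk", leads to a telephone assessment and then a discussion with the study coordinator. The condition for removal is: "If prolonged ICBT treatment is considered inappropriate with regard to the participants' best interest and well-being". The consequence follows in the same sentence: "well-being the participant is excluded from the study and both parent and adolescent provided with proper referral information". The removal is from the study, not only from ICBT.

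Section 3 (Ethical considerations) adds that regular contact "ensures that families with problems too severe for this program will be referred to more suitable treatments". That sentence speaks of referral and does not mention leaving the study.

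On outcome, section 1.1.2 states: "CY-BOCS will be the primary outcome measure". Section 1.2.8 places the post-treatment interview "latest within 4 weeks after treatment protocol is finished", and then: "Follow-up measurements will be performed at 3, 6 and 12 months after treatment". Neither sentence provides for someone taken off ICBT early. Section 1.4 describes an open trial with n=27, d=0.5, 80% power and p=.05.

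**The concern.** Stopping a treatment and ending observation are separate decisions. Here one safety judgement triggers both. It is made after treatment has begun and in response to how the participant is doing, so the resulting loss of CY-BOCS may depend on the outcome. In a randomised trial, a similar loss in the comparison arm might offset part of this. A single-arm pre-post comparison has no such offset.

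Efficacy, feasibility and acceptability are all stated objectives (section 2, Objective). Participants for whom ICBT proved unsuitable say much about each. Interviewees for the qualitative study are recruited during follow-up (section 1.2.8), so excluded participants would probably be missing there as well.

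This is a protocol matter. A SAP can define analysis sets and missing-data rules, but it cannot recover interviews that were never held.

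**Working it through.** **Inputs from the protocol (section 1.4).** n=27, d=0.5, 80% power, p=.05, one arm.

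**Assumptions.** d is read as mean change divided by the SD of change. Change scores are normal. The number excluded, k, is 2 or 3, because the protocol gives none.

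**The plan's own figure.** A one-sample t-test on change with d=0.5 and one-sided .05 needs n=27 (power 81.2%), so the stated size reproduces. Two-sided .05 would need 34, and power at 27 would be 70.6%.

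**Bias formula.** Suppose the k excluded participants average δ SD below the mean of all 27. The mean of those remaining is then too high by

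bias = k × δ / (27 − k).

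Four cases for δ, each with k=2 and then k=3:

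- *Exclusions unrelated to outcome:* δ=0, so the bias is 0.
- *Exactly the worst removed:* by simulation, the two lowest of 27 average 1.785 SD below the mean and the three lowest 1.62. Bias = 2×1.785/25 = 0.14 and 3×1.62/24 = 0.20.
- *Random draw from the worst third:* by simulation, the nine lowest average about 1.06 SD below the mean. Bias = 2×1.06/25 = 0.085 and 3×1.06/24 = 0.13.
- *Trigger correlated 0.3 with CY-BOCS change:* δ is 0.3 times the worst-removed value, that is 0.536 and 0.486. Bias = 2×0.536/25 = 0.04 and 3×0.486/24 = 0.06.

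As a cross-check, suppose the true mean is 0.50 SD and the excluded participants had no change at all. The remaining mean is 27×0.5/25 = 0.54 or 27×0.5/24 = 0.56, a bias of 0.04-0.06.

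**False-positive rate.** I simulated 200,000 trials of 27 changes with true mean zero and counted significant results in the direction of improvement at two-sided .05.

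| How the 2-3 excluded arise | Bias (SD) | False improvement |
|---|---|---|
| Unrelated to outcome | 0 | 2.5% |
| Trigger correlated 0.3 with change | 0.04-0.06 | 4-5% |
| Random from the worst third | 0.09-0.13 | 6-9% |
| Exactly the worst (upper bound) | 0.14-0.20 | 14-23% |

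Under the one-sided .05 test that reproduces n=27, the upper bound for k=2 and 3 is 22% and 33% against a nominal 5%.

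**Power.** Losing 2 or 3 participants lowers one-sided power at d=0.5 from 81.2% to 78.3% or 76.8%. This is minor beside the possible bias.

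**The case against.** Four stronger readings are tempting, and the protocol does not support them.

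- *A reader might infer that excluded participants drop out of the CY-BOCS analysis.* The protocol names no analysis set. That and the missing-data rule may be in a SAP not shown, and a conservative rule such as assuming no change could remove or reverse the bias. It would do so only by assumption, however: someone who worsened would be scored too favourably and someone who improved too harshly.
- *A reader might infer that these are the worst CY-BOCS outcomes.* The trigger is a threat to well-being, with suicide risk as the example. It is not a rise in CY-BOCS, and an adverse event does not lead automatically to exclusion. A link with poor CY-BOCS change is plausible but not shown.
- *A reader might infer that no analysis could help.* Child and parent CHOCI-R are collected weekly (section 1.2.5), and section 1.1.3 says the scale correlates with CY-BOCS. With the baseline CY-BOCS, this gives a course up to exit that can inform a model or a sensitivity analysis. It does not show what happens afterwards.
- *A reader might infer that harms go unreported.* Sections 1.1.3 and 1.2.6 both commit to publishing adverse events. Only harms after exit may be missed.

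It is also fair to say that the entry criteria already screen out suicidal ideation, psychosis, bipolar disorder and substance dependence, so exclusions may be few. Treatment is fixed at 12 weeks (section 1.2.4), so a due date can be derived for someone who stops early, although the protocol does not state it. The study is a pilot seeking preliminary effectiveness. These points limit the size and severity of the problem. They do not restore the CY-BOCS assessments that the exclusion rule ends.

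**Conclusion.** The point holds as a risk built into the wording. Section 1.2.6 ends collection of the primary outcome for participants selected by clinical course, in a design with nothing to offset the loss. Overstated improvement is the likely direction, but this is not established.

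The size cannot be fixed from the protocol. With no exclusions there is no bias. With 2 or 3 of 27 excluded, the range is 0 to 0.20 SD. The top of that range, 0.14-0.20 SD, equals 28-40% of the d=0.5 the trial is sized on (0.14/0.5 and 0.20/0.5). It requires the safety judgement to pick out exactly the worst CY-BOCS changes, so it is a bound and not an expectation. The middle cases, 0.04-0.13 SD, also rest on an assumed number of exclusions, and on an assumed link between trigger and outcome. All the figures describe an analysis restricted to participants with a post-treatment CY-BOCS, which the protocol neither states nor rules out.

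Severity: should be fixed.

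**What to change.** Leave the clinical decision to stop ICBT and refer exactly as it is. Change only what happens to observation:

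1. In section 1.2.6, replace exclusion from the study with wording that the participant stops ICBT but remains in the study for assessment unless consent is withdrawn.
2. In section 1.2.8, state that the post-treatment CY-BOCS, CGI and CGAS are due for everyone at 12 weeks from treatment start, with the same 4-week window, and count the 3-, 6- and 12-month contacts from there.
3. Report how many participants stopped ICBT, with reasons, and record any other care they received.

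The cost is a wording change and a few extra assessments. Follow-up clinician ratings are already done by telephone, and the post-treatment rating could be too where needed. The downside is that these participants may be receiving other care, so their later scores do not reflect ICBT alone; recording that care lets the reader judge.

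The protocol version is dated December 2014, while section 1.6 schedules the pilot for the first half of 2013. If that schedule held, post-treatment visits can no longer be added. The change would then apply to follow-up contacts still due and to the reporting of those who stopped.
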